## Abstract

This article aims to present the theoretical basis, methodology, and design of a clinical trial we will conduct. The study will be prospective, randomized, placebo-controlled, and double-blind. Each intervention period will last 8 weeks and the trial will be conducted on 100 patients in total, who will be randomly divided into two groups consisting of 50 patients each. We plan to investigate the impact of *Lactobacillus helveticus Rosell* and *Bifidobacterium longum Rosell* on the depressive, anxiety, and stress levels in patients with depressive disorders with possible comorbid anxiety. In addition to assessing the influence of probiotics on the clinical condition, we also plan to study the clinical and biochemical parameters of metabolic syndrome, which often coexists with depression. Both depressive and metabolic issues may have part of their etiopathology in common, e.g., inflammation, oxidative stress, and dysbiosis. This is why we will additionally investigate the parameters related to gut microbiota, inflammatory, and oxidative statuses. Thus, the primary endpoint of the study will be the change in depression score measured with the Montgomery–Åsberg Depression Rating Scale. The secondary endpoints will include changes in anxiety and stress levels, as well as metabolic, inflammation, and oxidative stress parameters.

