The aim of this study was to gather empirical evidence that will enable us to evaluate the impact of probiotic supplementation on the severity of anxiety and depressive symptoms, function and composition of gut microbiota, metabolic parameters, and inflammation and oxidative stress markers in patients with diagnosed depressive disorders.

Our scientific hypotheses were the following:-Comorbidity of anxiety symptoms in patients with diagnosed depressive disorders increases the likelihood of therapeutic response to probiotic supplementation in both depressive and anxiety symptoms;-Metabolic abnormalities, chronic inflammation, and oxidative stress markers may be predictive of probiotic efficacy toward depression;-Probiotic supplementation increases the concentration of fecal short-chain fatty acids and the level of diversity of gut microbiota composition in depressed subjects;-Probiotic supplementation improves metabolic parameters in patients with depressive disorders;-Probiotic supplementation improves inflammation and oxidative stress parameters in patients with depressive disorders;-Functional biomarkers (the ratio of levels of short-chain fatty acids) but not classification (taxonomic) changes of microbiota are typical for depressive disorders.

In our trial, the primary outcome measure will be the severity of depressive symptoms assessed with the Montgomery–Åsberg Depression Rating Scale (MADRS). The secondary outcome measures will include depression, anxiety, and stress symptoms assessed with the Depression, Anxiety, and Stress Scale (DASS) with subscale scores; the quality of life level assessed with the WHOQOL-BREF instrument; blood pressure (BP), body mass index (BMI), and waist circumference (WC) measures; and fasting glucose (fGlc), HDL cholesterol (HDL-C), triglycerides (TG), white blood cell count (WBC), neutrofiles, serum levels of C-reactive protein (CRP), levels of fecal SCFAs, fecal microbiota α-diversity, and the levels of oxidative stress parameters (total antioxidant capacity (TAC) and malondialdehyde (MDA)) in the blood serum (Table 1).

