#### Sample Size Calculation

As for the primary outcome of the study, namely, the MADRS score, we will use a standard deviation of 5.15 and a difference in the mean of 2.9 (M1 = 20.0, M2 = 17.1). We based our assumptions regarding the mean and standard deviation of MADRS in a depressed population on a study by Dijkstra et al. [49]. A difference in the MADRS of 2.2 points or higher seems clinically relevant (Cohen’s D has a value of 0.4, while a value of 0.4 or higher is widely considered to be associated with a clinically relevant effect size). Using an online tool (https://www.stat.ubc.ca/~rollin/stats/ssize/n2.html, accessed on 2 December 2022), we calculated the required sample size (assuming that both groups taking part in the study are the same size). The total sample size for this study should be around 100 (M1 = 20.0, M2 = 17.1, SD = 5.15, alpha = 0.05, power = 80%).

More details of sample size calculations for different secondary outcome measures are described in Appendix A.

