### 3.2. Design

The patients from the two clinical groups will undergo pharmacological and psychological treatment in compliance with the procedures of the clinic. It is worth mentioning that the researchers will at no stage interfere in the treatment process.

The patients will be recruited in the Central Teaching Hospital (inpatient and outpatient clinics), Medical University of Lodz, Poland.

We plan to measure the following metabolic parameters: blood pressure (BP), weight, body mass index (BMI), and waist circumference (WC). Blood samples of each patient will be collected to determine serum CBC and measure the levels of C-reactive protein, HDL cholesterol, triglycerides, and fasting glucose. Microbiota function (as SCFA concentrations in feces) and composition will be assessed. The oxidative stress level in the blood will be assessed as the total antioxidant capacity (TAC) and the level of malondialdehyde (MDA) concentration in blood plasma.

The patients will be observed for twenty weeks and they will be administered probiotic supplements for the first eight weeks.

The study will consist of the following visits:

V0 “recruitment visit”: assessment of inclusion and exclusion criteria, giving informed consent, a full psychiatric and somatic examination, filling in a survey questionnaire (SQ), and filling in the MADRS scale;

V1 “randomisation visit” (within 5 days following V0): filling in the DASS and WHOQOL-BREF scales; measuring BP, WC, and BMI; blood and stool collection; and • t1-t3:3/8 monitoring using personal contact via phone or e-mail every two weeks; 

V2 “final visit” after 8 weeks following V1: filling in MADRS, DASS, and WHOQOL-BREF scales; measuring BP, WC, and BMI; and blood and stool collection; 

V3 “follow-up visit” after 12 weeks following V2: filling in the SQ, MADRS, DASS, and WHOQOL-BREF scales and measuring BP, WC, and BMI.

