## Appendix A

Sample size analysis details:

The authors made an effort to determine the correct sample size for the study regarding the secondary endpoints.

As for CRP, the investigators in this study decided to use the number of participants needed to detect a mean difference between the groups in the hsCRP level of 2.0 mg/L (standard deviation 3.0 mg/L) at day 60 with 80% power and 95% confidence. The number of subjects needed was 20 per group. The range of values for the mean CRP and standard deviation in the group of depressed patients was indicated in the studies by Chamberlain et al. and Pitharouli et al. [76,77].

As for BMI, the sample size calculations were based on the assumption of a 2.0 kg/m^2^ reduction in BMI at day 60 in the probiotic group compared with the placebo group (M1 = 23.0, M2 = 21.0). A decrease in BMI by approximately 2 kg/m^2^ may significantly influence metabolic risk [78]. To detect this difference, assuming a common standard deviation of 3.0 using a two-group *t*-test with a 0.05 two-sided significance level, we estimated that a sample size of 20 subjects in the probiotic intervention group and 20 subjects in the placebo group would have 80% power.

As for the lipid profile, we determined that 16 participants in each study group (probiotic versus placebo) would be sufficient to detect a mean difference in LDL cholesterol of 0.45 mmol/L (M1 = 3.45 mmol/L, M2 = 3.0 mmol/L, SD = 0.6 mmol/L), with 80% power at *p* = 0.05. Hypothetical values were based on the data found in the study by Ivey et al. [79].

As for the first criterion of metabolic syndrome, namely, WC, we used a standard deviation of 8.5 and a difference in mean of 9.0 (M1 = 90.0 cm, M2 = 99.0 cm). We based our assumptions on a study by Niyonsenga et al. [80], which indicated a mean and standard deviation of WC in a depressed population. This calculation determined that 16 patients for each group were required to provide >80% power with *p* = 0.05.

As for HDL, we used a standard deviation of 11.6 and a difference in mean of 12.0 (M1 = 67.0 mg/dL, M2 = 55.0 mg/dL). We based our assumptions on a study by Martinac et al. [81], which provided a mean and standard deviation of HDL in a depressed population. This calculation determined that 16 patients for each group were required to provide >80% power with *p* = 0.05.

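### The primary endpoint is a change in MADRS in the abstract but a MADRS score in the text and sample size; one definition, week-8 MADRS by ANCOVA on the V0 score, would settle this and raise power at no real cost

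*Protocol article*

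**What the plan says.** The Abstract states that "the primary endpoint of the study will be the change in depression score" on MADRS. The Introduction, listing the outcomes, states instead that "the primary outcome measure will be the severity of depressive symptoms", again on MADRS. The section Sample Size Calculation names the MADRS score as the primary outcome and says "we will use a standard deviation of 5.15 and a difference in the mean of 2.9", with group means of 20.0 and 17.1 and "alpha = 0.05, power = 80"%. On the source of these figures it says: "We based our assumptions regarding the mean and standard deviation of MADRS in a depressed population". That describes the spread of a score at one time. No SD of change, correlation between visits or residual SD enters the calculation.

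Section 3.2 (Design) schedules MADRS at V0, at V2 (8 weeks after V1) and at V3 (12 weeks after V2). None of the statements of the primary outcome names a visit. Section 2.4 lists covariates (age, diet, BMI and others) in its microbiota paragraph; baseline MADRS is not among them.

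**The concern.** A score at week 8 and a change from baseline to week 8 have, under randomisation, the same expected difference between arms but different variances. The variance of change depends on how strongly the two ratings correlate; the variance of the score does not. A sample size worked out for one therefore does not carry over to the other without a statement about that correlation.

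If the abstract's endpoint were analysed as a raw change score, the stated 80% power could be too high or too low, and the article gives no means of telling which. If the score were analysed without adjustment, as it was sized, the V0 rating collected on every patient would add nothing to precision. Baseline adjustment avoids both problems.

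**Working it through.** **Inputs.** Difference 2.9, SD 5.15, alpha 0.05, power 80% (Sample Size Calculation); 50 per arm (section 3.1). The article does not state sidedness for MADRS. Two-sided is assumed because Appendix A uses a "two-group *t*-test with a 0.05 two-sided significance level" for BMI and because it reproduces the total; a one-sided test would need only 39 per arm. The correlation r between V0 and V2 MADRS is not given, so a range is shown.

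**1. The plan's own figure.** Normal approximation, two independent means:

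n per arm = 2 × (1.96 + 0.84)² × 5.15² / 2.9² = 49.5, rounded up to 50, or 100 in total.

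Power at 50 per arm is 80.4% by the normal approximation and 79.6% by the t distribution. The stated total is right for an unadjusted comparison of scores at one time.

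**2. Raw change score and ANCOVA with the same inputs.** Assume SD 5.15 at both V0 and V2.

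- SD of change = 5.15 × √(2(1 − r))
- Residual SD under ANCOVA = 5.15 × √(1 − r²)

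Power from the t distribution, 50 per arm, difference 2.9:

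| r | SD of change | Power, change | Residual SD | Power, ANCOVA |
|---|---|---|---|---|
| 0.3 | 6.09 | 65% | 4.91 | 83% |
| 0.4 | 5.64 | 72% | 4.72 | 86% |
| 0.5 | 5.15 | 80% | 4.46 | 90% |
| 0.6 | 4.61 | 88% | 4.12 | 94% |
| 0.7 | 3.99 | 95% | 3.68 | 97% |

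By the normal approximation, a raw change score needs a total of 140 at r = 0.3, 120 at r = 0.4, 100 at r = 0.5 and 80 at r = 0.6.

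**3. Where the break-even lies.** The variance of change is s0² + s2² − 2·r·s0·s2, where s0 and s2 are the SDs at V0 and V2. Setting it equal to s2² gives r = s0 / (2·s2). With equal SDs this is 0.5. Entry requires MADRS of at least 13, which may narrow the V0 distribution. With s2 = 5.15 and, purely as an illustration, s0 = 4.0, the break-even is 4.0 / 10.3 = 0.39.

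**4. Limits of the ANCOVA gain.** With 20% loss (40 evaluable per arm), t-based ANCOVA power is about 74% at r = 0.3, 77% at r = 0.4, 82% at r = 0.5 and 88% at r = 0.6, so r of about 0.45 or more is needed for 80%. For the 2.2-point difference that the article calls clinically relevant, with all 100 patients evaluable, power is about 56% unadjusted and, with ANCOVA, 60% at r = 0.3 and 68% at r = 0.5. It reaches 80% only at r of about 0.65.

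**The case against.** **An outcome measure and an endpoint can coexist.** The Introduction names an instrument and a construct, while the abstract names a quantity derived from them. The expected between-arm difference is the same for change and for final score, so 20.0 against 17.1 fits both. This softens the contradiction but leaves the variance open: the SD used is described as that of a score, and the 80% is shown only for a score.

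**The model may stand in the full protocol or analysis plan.** This is correct. The absence of baseline MADRS from the covariates in a condensed article is not a finding by itself. Sizing without adjustment is common and conservative even when ANCOVA is planned, and nothing here says that MADRS will be analysed unadjusted.

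**The primary visit can be inferred.** Supplementation ends at week 8, V2 is labelled the final visit and V3 a follow-up visit, and Appendix A sizes CRP and BMI at day 60. A reader might infer two chances at significance, V2 and V3, with type I error of about 8% to 10% if each were tested at 5%. The article proposes no such analysis, so that figure does not describe this plan.

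**The direction of the power error is unknown.** This also stands. Above the break-even correlation a raw change score has more than 80% power, and the break-even is 0.5 only if the two SDs are equal.

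**Conclusion.** The point holds as a mismatch of definition and sizing with a better method readily available. The stated 80% power belongs to a single-time comparison of MADRS scores. For the change endpoint of the abstract it is not established: it runs from about 65% at r = 0.3 to about 95% at r = 0.7, given equal SDs at V0 and V2, a difference of 2.9 and 50 evaluable patients per arm.

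Two stronger readings are tempting. One is that the sample size is wrong; it is not, since it reproduces for the comparison described. The other is that ANCOVA would secure 80% power. It is at least as efficient as either alternative, apart from one degree of freedom, but whether it reaches 80% depends on an r that the article does not give, on attrition for which the stated total shows no allowance, and on the true difference being 2.9 rather than 2.2. The change is a free improvement in clarity and efficiency.

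**What to change.** - Define the primary endpoint once: MADRS at V2 (week 8), compared between arms by ANCOVA with V0 MADRS as covariate, reported as the adjusted mean difference with 95% CI. With the baseline in the model, analysing change or score gives the same treatment estimate, so the two descriptions no longer conflict.
- Name MADRS at V3 (week 20) as secondary.
- Align the Abstract, the Introduction and the Sample Size Calculation with that definition. State there that 5.15 is taken as the SD of the week-8 score, and give the assumed r if any gain from adjustment is claimed.
- The same baseline-adjusted model can serve the secondary outcomes measured at both V1 and V2: DASS, WHOQOL-BREF, BP, BMI, WC and the laboratory measures.

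The cost is wording and one degree of freedom. V0 and V2 MADRS are already scheduled for every patient, so no patients, visits or assays are added.

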## 1. Introduction

Depression is one of the most common and debilitating disorders worldwide [1]. Moreover, depressive disorders often coexist with somatic diseases, further increasing mortality risks [2,3]. Recent studies uncovered that depression and other civilization diseases are associated with chronic, low-grade inflammation. This is characterized by increased circulating pro-inflammatory cytokines, altered leukocyte population frequencies in blood, and the accumulation of activated immune cells in tissues, including the brain [4]. Although far from conclusive, emerging evidence suggests that chronic inflammatory conditions in the central and peripheral immune systems may mediate a subset of depressive disorders [5] that are commonly concurrent with obesity. Several studies showed that oxidative stress (the imbalance between the production of free radicals and their neutralization by antioxidants), along with inflammation, leads to the development of depression and its comorbidities [6,7,8,9,10].

Elucidating these mechanisms linking depression, inflammation, and oxidative stress could generate potential new therapeutic targets or patient-specific strategies to combat both depressive disorders and their coexisting conditions.

Recently, there has been much interest in the role of intestinal microbiota changes in the pathophysiology of civilization diseases. The term “microbiota” refers to all microorganisms in a specific environment [11]. The intestines are where the microbiota population is most abundant in the human body [11]. Its basic functions include maintaining the integrity of the intestinal wall, protection against pathogenic bacteria and viruses, and the synthesis of key vitamins [11,12]. In addition, microbiota participates in the metabolism of nutrients, e.g., converts dietary carbohydrates into short-chain fatty acids (SCAFs)—namely, butyrate, acetate, and propionate—which are the most representative metabolites of anaerobic intestinal fermentation of fiber, and assessments of their level are used to analyze the function of the microbiome [13]. It was shown that the levels of SCFAs and the ratio of their three main components can also be good markers of intestinal dysbiosis and serve as a reliable approach to the assessment of microflora function [14]. There is more and more evidence showing that aberrant gut microbiota may lead to chronic inflammation [15,16] and oxidative stress exacerbation in tissues [17] and may serve as a link between depression and dysbiosis.

Experimental studies conducted in animal models over the past few years confirmed the relationship between dysbiosis (imbalanced microbiome) and depression-like behavior [18,19,20,21]. Similar relationships were observed in human studies. The results of the research revealed a clear diversification of the intestinal microflora (different types and species of bacteria) [22,23,24]. On top of that, patients diagnosed with major depressive disorder (MDD) show altered levels of butyrate, acetate, and propionate [25,26]. In the patients with higher amounts of butyrate-producing bacteria, such as *Faecali bacterium* and *Coprococcus* spp., the parameters of quality of life were more favorable [27]. It was also found that propionate administration alleviates depressive symptoms in mice [27]. The composition of the analyzed fecal microbiota, typically found in patients with depressive disorders, is heterogenous [22,23,24]. The functional level of the gut ecosystem is mostly independent of the taxonomic order, and a taxonomic approach alone is unlikely to be sufficient to reliably assess the health and function of the microbiota [28]. Thus, microbiota composition and fecal SCFA levels will be investigated in the study. 

The administration of probiotics (live microorganisms intended to provide health benefits to the host when administered) is one of the methods of modifying disturbed microbiome imbalance [29]. Recent studies, including two meta-analytical summaries, emphasized the beneficial role of probiotic supplementation and the reduction in the severity of depressive symptoms in patients with mild or moderate depressive episodes [30,31]. However, the number of studies that assessed the role of probiotic supplementation in patients with the above diagnosis remains insufficient and of various designs. More research on patients with anxiety and depression symptoms is necessary, as most of the interventions were carried out on mentally healthy individuals.

What is particularly interesting for us in the context of the project. Some studies were focused on assessing the potential impact of probiotic supplementation on the symptoms of anxiety coexisting with depression [32,33]. However, these studies yielded conflicting results. In some of them, probiotic supplementation (lasting from 8 to 12 weeks) reduced anxiety symptoms, while in other studies and two meta-analytical summaries, probiotic supplementation did not significantly affect anxiety symptoms in humans, but decreased their severity in animals [34,35]. Bearing in mind the inconclusive results of previous research, we plan to investigate these issues in depth. Furthermore, depression with anxiety features and mixed depressive and anxiety disorder (MDAD) are now integral parts of the depressive disorders section of the International Classification of Diseases (ICD-11).

According to recent research, probiotic supplementation, which provides a reduction in intestinal dysbiosis with immunomodulatory and anti-inflammatory effects, may also help to treat metabolic abnormalities. The latest meta-analysis of probiotic supplementation’s impact on metabolic syndrome parameters indicated an improvement in the body mass index (BMI), lipid profile, and glucose metabolism [36,37]. Moreover, probiotic supplementation may have a positive effect on the parameters of inflammation and oxidative stress [38,39]. There are only a few studies on this subject available, in which malondialdehyde’s (MDA) serum level was significantly decreased, while the total antioxidant capacity (TAC) remained unchanged [40] during probiotics supplementation. Malondialdehyde is one of the final products of polyunsaturated fatty acid peroxidation in the cells and has a mutagenic and carcinogenic effect [41]. Total antioxidant capacity (TAC) is a popular diagnostic test that is frequently used to assess the antioxidant status of biological samples and can estimate the antioxidant response against the free radicals produced in the organism. Thus, we intend to observe some of the metabolic, inflammatory, and oxidative parameters during probiotics supplementation; these issues have not been studied thoroughly so far. It may help to distinguish the subpopulation of depressed subjects that responds positively to probiotic supplementation, as well as some biomarkers of probiotics efficacy in depression.

The aim of this study was to gather empirical evidence that will enable us to evaluate the impact of probiotic supplementation on the severity of anxiety and depressive symptoms, function and composition of gut microbiota, metabolic parameters, and inflammation and oxidative stress markers in patients with diagnosed depressive disorders.

Our scientific hypotheses were the following:-Comorbidity of anxiety symptoms in patients with diagnosed depressive disorders increases the likelihood of therapeutic response to probiotic supplementation in both depressive and anxiety symptoms;-Metabolic abnormalities, chronic inflammation, and oxidative stress markers may be predictive of probiotic efficacy toward depression;-Probiotic supplementation increases the concentration of fecal short-chain fatty acids and the level of diversity of gut microbiota composition in depressed subjects;-Probiotic supplementation improves metabolic parameters in patients with depressive disorders;-Probiotic supplementation improves inflammation and oxidative stress parameters in patients with depressive disorders;-Functional biomarkers (the ratio of levels of short-chain fatty acids) but not classification (taxonomic) changes of microbiota are typical for depressive disorders.

In our trial, the primary outcome measure will be the severity of depressive symptoms assessed with the Montgomery–Åsberg Depression Rating Scale (MADRS). The secondary outcome measures will include depression, anxiety, and stress symptoms assessed with the Depression, Anxiety, and Stress Scale (DASS) with subscale scores; the quality of life level assessed with the WHOQOL-BREF instrument; blood pressure (BP), body mass index (BMI), and waist circumference (WC) measures; and fasting glucose (fGlc), HDL cholesterol (HDL-C), triglycerides (TG), white blood cell count (WBC), neutrofiles, serum levels of C-reactive protein (CRP), levels of fecal SCFAs, fecal microbiota α-diversity, and the levels of oxidative stress parameters (total antioxidant capacity (TAC) and malondialdehyde (MDA)) in the blood serum (Table 1).

